### 2.3 Primary analysis

The rate of responders to treatment was reported for each treatment group. The primary effect estimate was the relative risk of response, reported with 95% confidence intervals (CI). The absolute difference and 95% CI was also reported. The rate of responders to treatment was compared between the treatment groups using unadjusted chi-squared test (or Fisher's exact test, as appropriate).

### 2.4 Secondary analyses

Multiple logistic mixed regression was used to identify relevant covariates in the mITT population anticipated with the primary outcome (criterion for entering variables was  $P < 0.10$ ), in addition to the stratification variables (centre):

- Categorical covariates
  - Gender (M/F)
  - Type of IBS (diarrhoea, constipation and mixed)
  - Ongoing analgesic treatments for IBS at inclusion (Y/N)
- Continuous covariates
  - Age (years)
  - IBS Duration (months)
  - Pain intensity (treated as continuous variable and then categorized as ordinal covariate  $\leq 3/10$ ,  $4-6/10$ ,  $\geq 7/10$ ).

Adjusted analyses was performed with the use of robust random-effect Poisson generalized linear mixed model regression with robust variance for binary outcomes, with centre as a random effect. Particular attention was paid to multicollinearity using the Farrar-Glauber test and variance inflation factor (VIF). The Akaike information criterion and Bayesian information criterion were calculated and used as model diagnostics to determine how well the model fit improved following addition of covariates. Significance of the intervention was assessed based on p-values and risk ratios with 95% CIs calculated from this regression.

Dichotomous secondary endpoints were compared using chi-squared test. Continuous variables were presented as mean and standard deviations (as median and quartiles, otherwise) and were compared with the use of the unpaired *t* test or the Mann-Whitney U test when appropriate (the Shapiro-Wilk test was used to assess normality, and the Fisher-Snedecor test to assess homoscedasticity). Adjusted analyses were performed with the use of robust random-effect Poisson generalized linear mixed model regression with robust variance for binary outcomes, multinomial logistic mixed model for categorical outcome, and linear mixed regression for continuous outcomes, with site as a random effect. Results were presented as absolute differences and risk ratios with CIs for binary and categorical data and between-group difference with CIs for continuous data.

Longitudinal analyses concerning repeated measures were studied using random-effect models (linear or generalized linear), to take into account patient as random-effect (slope and intercept), nestled in center random-effect.

Planned subgroup analyses were assess heterogeneity of the effect of ethosuximide on the primary outcome measure in pre-specified subgroups of patients with IBS subgroup and gender. According to usual recommendations, the interactions between group randomization and subgroups was evaluated in regression models (i.e., random-effects models, linear or generalized linear).

A descriptive analysis of stopping and discontinuations in view of dose escalation was considered. A particular focus was done to safety and lose to follow-up. A study of abandonment considered as censored data was proposed using the Kaplan-Meier estimation. The proportional-hazard hypothesis was verified using Schoenfeld's test and plotting residuals.

Finally, a sensitivity analysis was performed and the nature of missing data was studied (missing at random or not). According to this, the most appropriate approach to the imputation of missing data was proposed (MICE, spline interpolation, LOCF, BOCF...).

A two-sided P value of less than 0.05 was considered for statistical significance of all analyzes. The Hochberg procedure was used to adjust for multiple testing of each component of the composite primary outcome ((1) decrease of at least 30% of the intensity of abdominal pain (11-point NRS) compared with the score before treatment and (2) significant global improvement defined by a score of 4 or 5 on the SGA scale). Because of the potential for type 1 error due to multiple comparisons, findings from analyses of secondary endpoints were interpreted as exploratory.

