##### *Statistical methods*

Statistical analyses will be conducted using Stata software (version 13, StataCorp, College Station, US). A two-sided p-value of less than 0.05 will be considered to indicate statistical significance (except interim analysis).

Intent-to-treat (ITT), mITT, and per-protocol (PP) analyses were performed for the primary endpoint and expressed as relative risks (RR) with 95% confidence intervals (CI). Non-compliant patients were considered non-responders. Responder rates were compared using the chi-squared test and a pre-specified multivariate analysis was performed using a generalized linear mixed model (Poisson regression with a log link and robust variance 26) accounted for fixed covariates (e.g., gender, IBS subtype) and centre-level variability were performed. Primary endpoint components were also analysed with the Hochberg procedure for multiple testing.

Continuous outcomes were assessed with linear mixed models incorporating patient-level random effects (slope and intercept) nested within centre-level random effects. Results were expressed as regression coefficients (standardized mean differences - MD) with 95% CI, based on the interaction between time and randomization group. The normality of residuals from these models was analysed as aforementioned. Safety analysis was conducted with chi-squared or Fisher's exact tests.

Missing data (if any) were imputed using Multiple Imputation by Chained Equations (MICE). Analyses were conducted using Stata 15.0, with a two-sided P value <0.05 considered significant, and the widths of confidence intervals were not adjusted for multiplicity and should not be used as a substitute for hypothesis testing, except for the primary outcome and its composite components. An interim analysis is planned after enrolment of the first 100 patients using the Lan and DeMets rule (East software, Cytel Inc, Cambridge, Massachusetts, US). The type I error is fixed at 0.03 for this interim analysis. In addition, an early intermediate analysis (third of the inclusions) will be also proposed in order to study safety of the initial maximum dose (10 ml/day) and, if necessary, to allow the addition of a therapeutic dose in case of inefficiency.

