### 1.8 Primary outcome measure

The primary outcome was the rate of responders to treatment: a patient will be considered as a responder if he satisfies two conditions: (1) a decrease of at least 30% of the score of abdominal pain (11-point NRS) compared with the score before treatment, and (2) a significant global improvement defined by a score of 4 or 5 on the SGA scale.

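### The adjusted responder analysis takes AIC, BIC and the centre variance from a Poisson likelihood on yes/no data; the robust variance does not correct these (minor)

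*Combined protocol and SAP*

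**What the plan says.** The outcome is binary (SAP 1.8): "The primary outcome was the rate of responders to treatment".

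SAP 2.4 builds the adjusted analysis in three steps.

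- Screening: "Multiple logistic mixed regression was used to identify relevant covariates in the mITT population", with entry at P < 0.10.
- Model: adjusted analyses use "robust random-effect Poisson generalized linear mixed model regression with robust variance for binary outcomes, with centre as a random effect". The same model is named again later in 2.4 for binary secondary endpoints, with site as the random effect.
- Fit and inference: "The Akaike information criterion and Bayesian information criterion were calculated and used as model diagnostics to determine how well the model fit improved" as covariates are added, and then "Significance of the intervention was assessed based on p-values and risk ratios with 95% CIs calculated from this regression".

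The protocol (Statistical methods) gives the same model as a pre-specified analysis of responder rates: "Poisson regression with a log link and robust variance", which "accounted for fixed covariates (e.g., gender, IBS subtype) and centre-level variability were performed".

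The primary comparison is separate. Under SAP 2.3, response rates are "compared between the treatment groups using unadjusted chi-squared test".

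**The concern.** Poisson regression with a robust variance is a legitimate way to obtain a risk ratio from binary data, because the sandwich estimator replaces the wrong Poisson variance when standard errors are computed. It replaces nothing else. Two quantities that SAP 2.4 relies on come straight from the likelihood.

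- AIC and BIC. The Poisson likelihood understates how much a covariate improves the fit to 0/1 data, while the penalty stays the same. The criteria become stricter than they should be.
- The centre variance. The Poisson model expects more chance scatter between centres than binary data can produce. Real differences between centres are put down to chance, and the variance is pulled towards zero.

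At stake is whether the secondary adjusted analysis is what the plan describes: covariates judged by a sound fit criterion, and the stratification factor allowed for.

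**Working it through.** **Inputs from the documents.** Response 35% on placebo and 55% on ethosuximide (protocol, Sample size), so 45% pooled with 1:1 allocation (SAP 1.4). 130 evaluable patients per group, 260 in total (SAP 1.7). At least ten sites (protocol, Enrolment). Randomisation stratified by centre with blocks of 6 (SAP 1.4).

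**Assumptions.** The documents give no centre heterogeneity, centre sizes or covariate effects. I take 10 centres of 26 and show a range of centre SDs on the logit scale.

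**The plan's own figure.** The pooled two-proportion formula for 35% against 55%, two-sided 5%, 90% power, gives 128 per group. With 130 per group, power is 90.5%. 130/0.9 = 144.4, hence 145 per group and 290 in total. The sample size reproduces.

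**Step 1: the variance.** Poisson assumes p = 0.45. Binary data have p(1-p) = 0.45 × 0.55 = 0.25. For a covariate with no effect, the Poisson likelihood-ratio statistic therefore behaves like (1-p) × chi-squared(1), here 0.55 × chi-squared(1).

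**Step 2: effective thresholds for one parameter.**

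| Criterion | Penalty | Correct likelihood | Poisson: penalty/0.55 | Effective p |
|---|---|---|---|---|
| AIC | 2 | p < 0.157 | 3.64 | p < 0.057 |
| BIC | ln 260 = 5.56 | p < 0.018 | 10.11 | p < 0.0015 |

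With treatment in the model the factor is (0.35 × 0.65 + 0.55 × 0.45)/(0.35 + 0.55) = 0.475/0.90 = 0.528, and the AIC threshold is about 0.052. In 1,000 simulated trials (centre SD 0.4), AIC credited a null covariate in 5.2% of Poisson fits and 17.9% of logistic fits.

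**Step 3: set against the P < 0.10 entry rule.** Under the correct likelihood, AIC (0.157) does not contradict a covariate entered at P < 0.10. Under Poisson it can, for p between about 0.057 and 0.10. For a real binary covariate (assumed log odds ratio 0.7) that had passed the screen, Poisson AIC showed no improvement in 10-13% of trials and logistic AIC in none. For BIC the figures were 66-71% and 24-26%.

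**Step 4: why the centre variance is pulled down.** For a centre of 26 at 45%, the Poisson model expects chance variance of 1/(26 × 0.45) = 0.085 in the log response rate. Binary data give 0.55/(26 × 0.45) = 0.047. The gap is 1/26 = 0.038, and roughly this much real centre variance is absorbed as chance. The true log-risk variance at logit SD 0.3, 0.5 and 0.8 is 0.025, 0.071 and 0.186. The first is below 0.038. Mean Poisson estimates over 300 simulated trials per setting were 0.004, 0.025 and 0.096.

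**Step 5: how often the centre variance is near zero.** 1,200 trials per setting, blocks of 6:

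| Logit SD | Poisson, 35% vs 55% | Logistic, 35% vs 55% | Poisson, no effect | Logistic, no effect |
|---|---|---|---|---|
| 0.3 | 84% | 34% | 82% | 31% |
| 0.5 | 51% | 9% | 41% | 9% |
| 0.8 | 13% | 1% | 10% | 1% |

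In a separate run at SD 0.4 the figures were 71% against 17% with 10 centres of 26, and 82% against 19% with 15 centres of 18.

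**Step 6: what happens to the treatment effect.** With a log link and exact balance within centres, the Poisson treatment coefficient equals the crude log risk ratio whether centre is omitted or fitted as a fixed factor. Blocks of 6 within centre come close to that. Over 1,500 trials, the empirical SD of the log risk ratio without centre and with fixed centre was:

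- SD 0.3: 0.1437 and 0.1434
- SD 0.5: 0.1441 and 0.1440
- SD 0.8: 0.1461 and 0.1460

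In a further comparison that included the random-effect model, the spread was the same (0.138) with centre omitted, random or fixed. The robust standard error also does its job: at centre SD 0.4 its mean was 0.137 against an empirical 0.138, while the model-based one was 0.189.

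**The case against.** The strongest reply is that little follows from this. Much of it stands.

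- The adjusted model is secondary. The primary test is an unadjusted chi-squared test with an unadjusted risk ratio, and neither uses the Poisson model.
- A reader might infer that a vanishing centre variance costs precision or power. It does not: step 6 shows the spread of the estimate is unchanged, because randomisation is stratified by centre. A model with no centre term can report a larger standard error than a fixed-centre one, but that is a difference in the reported figure, not in actual precision.
- A reader might also infer that AIC and BIC will throw out real covariates. SAP 2.4 calls them diagnostics and states no cut-off and no rule for dropping a covariate. Entry is by P < 0.10. Nor does it name the model they are computed on. The Poisson model is the natural reading, since the sentence stands between that model and the reference to this regression.
- A correct BIC (p < 0.018) is already stricter than the P < 0.10 screen, so part of that mismatch has nothing to do with Poisson.
- The frequency of a zero centre variance depends on heterogeneity the documents do not give, and the logistic model also returns zero fairly often when heterogeneity is small. The excess over logistic is the figure that counts.

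What the reply does not remove: the log-likelihood and the centre variance are wrong for binary data, and neither document takes them from a Bernoulli likelihood.

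**Conclusion.** The point holds, as a minor one. On the Poisson model, AIC and BIC are the wrong yardstick: about p < 0.057 instead of 0.157, and p < 0.0015 instead of 0.018. This follows from the planned response rates and n = 260 and needs no assumption about centres. AIC can therefore report no improvement for a covariate that the same section has just entered.

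The centre adjustment promised in both documents is often not in effect. The centre variance is near zero in about 80-85%, 40-50% and 10-15% of Poisson fits at logit SD 0.3, 0.5 and 0.8, against about 30-35%, 10% and 1-2% of logistic fits. These figures rest on the assumed 10 centres of 26.

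The documents do not support the stronger reading that the adjusted risk ratio is biased, that its robust interval is invalidated by this, or that the trial loses power. The harm is confined to a fit criterion and a centre term in a secondary analysis.

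**What to change.** In SAP 2.4, with matching wording in the protocol's Statistical methods:

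- State that AIC and BIC are computed only from the logistic mixed model already used for screening, and not from the Poisson model. It would help to add whether they decide anything or are only reported.
- For the adjusted risk ratio, choose one of two routes. Either keep the robust Poisson model but enter centre as a fixed factor with patient-level robust variance, merging very small centres; or obtain the risk ratio and risk difference by standardisation from the logistic mixed model. Apply the same choice to binary secondary endpoints.

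The cost is a few sentences and a few lines of code, with no new data or patients. The fixed-factor route adds about nine centre terms. In simulation its type I error was 5.1-5.7%, against 6.9-8.2% for the random-effect Poisson model with centre-clustered robust errors and a normal reference. The SAP does not state the level of clustering, and that contrast reflects the small number of centres, a separate matter.

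The fixed-factor route should not be presented as a gain in precision. At 35% against 55% its reported standard error was somewhat below the empirical spread (0.1398 against 0.144 at SD 0.5; 0.1357 against 0.146 at SD 0.8).

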#### Sample size:

According to previous work presented in literature, we have estimated that a sample size of  $n = 130$  patients per randomized group, for a two-sided type I error at 5%, would provide 90% statistical power of detecting an absolute difference of 20% between ethosuximide and placebo in the primary outcome: rate of responders to treatment as defined previously (35% for placebo and 55% for ethosuximide). Finally, a total of  $n=290$  patients (145 by group) will be considered to take into account lost to follow-up (10%). An interim analysis will be performed after 100 included patients to analyse safety and effectiveness in order to recalculate the sample size according results.

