#### Enrolment:

At least ten clinical sites participate in France, all specialized in the treatment of IBS. The recruitment will be spread over 30 months with 1 patients/month/centre, which seems to be largely sufficient in the recruitment potential (prevalence of IBS = 15% in French population []).

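### Adjusted risk ratios: the robust variance is not specified, and its natural centre-level form is too small with about ten centres

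*Combined protocol and SAP*

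**What the plan says.** SAP 2.4 (Secondary analyses) fits adjusted binary outcomes by "robust random-effect Poisson generalized linear mixed model regression with robust variance for binary outcomes, with centre as a random effect". It then gives that model an inferential role: "Significance of the intervention was assessed based on p-values and risk ratios with 95% CIs calculated from this regression". The protocol's Statistical methods section describes the adjusted comparison of responder rates, which it calls pre-specified, as a "generalized linear mixed model (Poisson regression with a log link and robust variance 26", allowing for covariates and centre.

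Neither document says whether the robust variance is summed over patients or over centres, whether tests use a normal or a t distribution, or whether a small-sample correction applies.

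On the number of centres, the protocol's Enrolment section says "At least ten clinical sites participate in France" and "The recruitment will be spread over 30 months with 1 patients/month/centre". Randomisation is 1:1 by patient, stratified by centre, in blocks of 6 (SAP 1.4).

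The primary comparison is an unadjusted chi-squared or Fisher test (SAP 2.3). For subgroups, SAP 2.4 says that "the interactions between group randomization and subgroups was evaluated in regression models", described only as random-effects models, linear or generalized linear.

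**The concern.** A sandwich variance is reliable when it adds up many independent terms. In a model with a random centre intercept, patients in one centre share an unobserved term, so the independent units of the likelihood are the centres. The sandwich that belongs to this model therefore has about ten terms. Such a variance tends to be too small and is itself imprecise, and a critical value of 1.96 allows for neither.

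Dropping the robust step is no remedy, because the Poisson variance overstates the variance of a 0/1 outcome. The result therefore depends on exactly the detail that the plan leaves out.

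At stake is the reading of the adjusted responder risk ratio. A non-significant primary chi-squared test could stand beside an adjusted ratio whose p-value is below 0.05 only because of the variance formula.

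**Working it through.** **Inputs from the documents.** 290 patients (145 per group); placebo response 35%, ethosuximide 55%; two-sided 5%; power 90%; 10% loss; at least ten centres; 30 months at one patient per month per centre; blocks of 6 within centre. **Assumptions, not in the documents:** between-centre SD on the logit scale (0 to 0.8 tried), balance of centre sizes, and covariate effects.

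**1. The plan's own figure.** n per group = [1.960 × √(2 × 0.45 × 0.55) + 1.282 × √(0.35 × 0.65 + 0.55 × 0.45)]² / 0.20² = (1.379 + 0.883)² / 0.04 = 128. At 130 per group, power is 90.5%. Loss: 130 / 0.90 = 144.4, so 145 per group and 290 in all. The sample size reproduces and is not in question.

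**2. Number of centres.** 10 × 30 × 1 = 300, against a target of 290; 290 / 30 = 9.7. Ten is the stated minimum and also the number that the accrual rate implies.

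**3. Why the terms are centres.** Centre j contributes L_j = ∫ ∏_i f(y_ij | b) φ(b) db, with score U_j. The sandwich is V = H⁻¹ (Σ_j U_j U_jᵀ) H⁻¹ × G/(G − 1), with the sum over G centres. As an approximation, the estimate divided by its standard error follows t on G − 1 degrees of freedom. A test at 1.96 then has type I error of about P(|t| > 1.96) on G − 1 df.

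**4. Size under no treatment effect, nominal 5%.** The random-intercept Poisson model was simulated with a centre-level sandwich and a normal reference. Set 1: 5000 trials per setting, response 35%, SD 0.4, seven covariates. Set 2: 3000-4000 trials, response 35%, SD 0.3 (0 in one run), with and without covariates. Set 3: a further run of the same comparison. Monte Carlo standard error is about 0.4-0.5 points in sets 1 and 2, for example √(0.09 × 0.91 / 4000) = 0.0045.

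| Centres | t approximation | Same, without G/(G − 1) | Set 1 | Set 2 | Set 3 |
|---|---|---|---|---|---|
| 10 | 8.2% | 9.6% | 8.1% equal, 9.5% unequal | 8.8-9.5% | 7.6-7.8% |
| 12 | 7.6% | 8.7% | 7.3% | 8.3% | – |
| 15 | 7.0% | 7.9% | 7.8% | 8.1% | 6.2% |
| 20 | 6.5% | 7.1% | 6.6% equal, 7.8% unequal | 6.7% | 5.8% |

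At ten centres the simulated range is 7.6-9.5%, so coverage is 100 − 9.5 = 90.5% to 100 − 7.6 = 92.4%. The between-centre SD matters little: in set 1 with ten centres, SD 0 gives 8.6% and SD 0.8 gives 8.1%.

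**5. Without the robust step.** At 35% response the Poisson variance exceeds the binary one by 1 / 0.65 = 1.54, so the standard error is √1.54 = 1.24 times too large. The error is then P(|Z| > 1.96 × 1.24 = 2.43) = 1.5%. Simulation gives 1.0-2.0%.

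**6. Alternatives.**
- Fixed centre terms with patient-level robust variance: 4.5-5.6% (set 1), 4.8-5.6% (set 3).
- Patient-level robust variance without centre terms, ten centres: 4.6-5.1% (set 2).
- Centre-level sandwich with t on G − 1 df: 5.7-6.2% at ten centres (set 2), 4.2-4.7% (set 3).

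**7. Interactions, only if the same model is used (set 1 settings, 3000 trials).** The 2-df IBS-type test rejects 12.3%, 8.7% and 7.6% of the time with 10, 15 and 20 centres; the gender test rejects 7.6%, 7.0% and 6.3%. With fixed centre terms and patient-level variance both lie at 3.8-4.6%.

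**The case against.** The strongest reply is that the plan does not say that the variance is clustered by centre. If a patient-level variance was intended, the error is about 5% and there is no inflation. The protocol's citation cannot settle this, because number 26 in its reference list is an animal study of chemotherapy-induced neuropathy. This stands: the plan cannot be said to commit to an anticonservative test. But the centre-level sum is the one that follows from the named likelihood, so the silence needs filling on either reading.

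Second, ten centres is a minimum. This also stands; the inflation shrinks with 15-20 centres but does not disappear.

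Third, the adjusted model sits among secondary analyses. Dichotomous secondary endpoints also have an unadjusted chi-squared test, and SAP 2.4 treats secondary-endpoint findings as exploratory. That limits the consequence. The exploratory label does not, however, expressly cover the adjusted analysis of the primary endpoint, and the SAP applies P < 0.05 to all analyses.

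Fourth, the simulations are not the exact planned analysis. They use all 290 patients and do not select covariates at P < 0.10 in the mITT population. The ranges are therefore approximate, although the mechanism depends on the number of centres and not on these details.

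**Conclusion.** The point holds as a gap in specification whose natural filling is anticonservative. If the robust variance is summed over centres and read against a normal distribution, the nominal 5% test of the adjusted risk ratio has type I error of roughly 7.5-9.5% with about ten centres (coverage about 90.5-92.5%), falling to roughly 6-8% with 15-20. These figures rest on the assumed response rate, centre variation and centre sizes; results changed little over the values tried.

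A reader might infer three stronger things that the documents do not support:
- **That the primary result is at risk.** It is not. SAP 2.3 uses an unadjusted chi-squared or Fisher test, and the sample size reproduces.
- **That the planned intervals are certainly too narrow.** The clustering level and reference distribution are unstated, and other choices give about 4-6%.
- **That the subgroup interaction tests are inflated, up to 12.3% for IBS type.** The SAP does not tie those tests to the Poisson model with robust variance, so the figure applies only if that model is used.

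**What to change.** In SAP 2.4 and the protocol's Statistical methods section, choose one of the following and state it in the same terms in both:

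- **(a)** Keep the random centre effect. State that the robust variance is clustered by centre, with a named small-sample correction, and that tests and intervals use a t (or F) reference on number of centres minus one degrees of freedom.
- **(b)** Use Poisson regression with log link, centre as fixed indicator terms, and patient-level robust variance. Patients are randomised individually within centre, so the design does not require clustering by centre. If small centres are pooled, set the rule by centre size only. Pooling according to observed response would make the model depend on the outcome.

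Apply the same choice to the subgroup interactions if they use this model, and say whether they do.

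The cost is wording and a changed model command, with no extra patients or data. Under (a) with ten centres, the t reference alone widens intervals by 2.262 / 1.960 = 1.15. Under (b) about nine degrees of freedom go to centre.

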### *Visit 2 - Start treatment (D0)*

Daily average abdominal pain scores have to be filled-in by the patient on the logbook during the last 7 days and the average abdominal pain score should be  $\geq 4$  to include the patient in the study. The patients have to fill-in three questionnaires: 1) IBS-SSS, 2) EQ-5D and 3) GIQLI.

If all the inclusion and non-inclusion criteria are conformed, the patient will be enrolled in the study and randomised in one of the two treatment arms (ethosuximide or placebo). The administration dosages, according to a specific titration regimen, will be explained in details to the patient. At the end of the visit, the patient will receive all the therapeutic units for the duration of administration required by the study protocol (4 weeks) and the daily logbook.

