### 1.4 Randomization

After patient informed consent was obtained and eligible criteria respected, enrolled patients were randomly allocated to receive either ethosuximide or placebo in a 1:1 ratio. Randomisation was conducted over a dedicated, password-protected, SSL-encrypted website (CSOnline, Clinsight) to allow concealed allocation. Each patient was given a unique patient number and randomisation number.

Computer-generated random numbers was used to generate allocation sequence with stratification by centre and a 6-block random sequence. Sequentially numbered containers were used to implement the random allocation sequence.

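### Continuous secondary outcomes have a pre-tested t or rank test, an unspecified adjusted model and a time-by-group interaction, with no own-baseline covariate or week-12 contrast named

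*Combined protocol and SAP*

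**What the plan says.** **Data.** At D0 the protocol (Visit 2) states: "The patients have to fill-in three questionnaires: 1) IBS-SSS, 2) EQ-5D and 3) GIQLI". Visits 3, 4 and 5 repeat them at weeks 4, 8 and 12, so each outcome has its own baseline and three follow-up values.

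**Analyses.** Three are described for continuous outcomes:

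1. SAP 2.4, unadjusted: an unpaired t test "or the Mann-Whitney U test when appropriate (the Shapiro-Wilk test was used to assess normality", with a Fisher-Snedecor check of equal variances. The SAP does not say whether the value compared is the week-12 score or the change from D0.
2. SAP 2.4, adjusted: a linear mixed regression with site as random effect. No fixed covariates are listed for it. The section's only covariate list is introduced for the primary outcome; it includes pain intensity but no baseline questionnaire score.
3. Protocol, Statistical methods (and the longitudinal paragraph of SAP 2.4): mixed models with patient random intercept and slope within centre. The protocol's results are "based on the interaction between time and randomization group". The coding of time, and whether D0 is a response in the model, are not stated.

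**Effect measure.** SAP 2.4 promises a between-group difference with its confidence interval. The protocol calls the result a standardised mean difference. The end of SAP section 2.4 treats secondary findings as exploratory.

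**The concern.** IBS severity and quality of life are named secondary objectives, yet none of the three analyses is designated as the result. Each has its own weakness.

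- The pre-test lets the data decide whether the unadjusted comparison concerns means or rank ordering. A Mann-Whitney p-value does not correspond to the between-group difference and interval that the SAP promises.
- An unadjusted week-12 comparison discards a baseline that is already collected.
- An interaction with linear time estimates a rate of divergence, not the week-12 difference. The protocol escalates dose over the first four weeks, so an effect that rises early and then holds is plausible, and a straight line fits that shape badly.

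At stake are the width of the intervals for these outcomes and whether the reported figure is the treatment difference at week 12.

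**Working it through.** **The plan's own figure.** The protocol's Sample size section gives 130 "patients per randomized group, for a two-sided type I error at 5%, would provide 90% statistical power", for "35% for placebo and 55% for ethosuximide". The pooled formula gives n = [1.960 x sqrt(2 x 0.45 x 0.55) + 1.282 x sqrt(0.35 x 0.65 + 0.55 x 0.45)]^2 / 0.20^2 = 128 per group. Power at 130 is 90.5%, and 130 / 0.90 rounds up to 145. The figure reproduces, but it concerns the primary outcome only. No power is stated for the questionnaires, so 130 per group is used below for illustration.

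**Precision.** The correlation rho between baseline and week 12 is not in the documents and is assumed to lie between 0.3 and 0.7. In outcome SD units, with 130 per group:

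- unadjusted week-12 test: SE = sqrt(2/130) = 0.124
- ANCOVA on own baseline: SE = sqrt((2/130) x (1 - rho^2))
- variance ratio, unadjusted to ANCOVA: 1 / (1 - rho^2)
- slope x 12 with D0 as a response, under compound symmetry: SE = sqrt((2/130) x 144(1 - rho)/80)

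| rho | SE unadjusted | SE ANCOVA | Variance ratio | ANCOVA CI narrower by | SE slope x 12 |
|---|---|---|---|---|---|
| 0.3 | 0.124 | 0.118 | 1.10 | 5% | 0.139 |
| 0.5 | 0.124 | 0.107 | 1.33 | 13% | 0.118 |
| 0.7 | 0.124 | 0.089 | 1.96 | 29% | 0.091 |

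For an assumed effect with 80% power in the t test, (1.960 + 0.842) x 0.124 = 0.347 SD, ANCOVA has power of 84%, 90% and 97.5%. The expected week-12 difference is the same with or without the covariate.

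**Linear time.** Suppose time enters as a number and D0 is a response. With times 0, 4, 8 and 12, the deviations from the mean are -6, -2, 2 and 6, with sum of squares 80. In a balanced random intercept-and-slope model, the fitted slope equals the least-squares slope. Let d be the true week-12 difference.

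For an effect reached by week 4 and held (0, d, d, d):

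- slope = (-2 + 2 + 6)d / 80 = 0.075d per week, so slope x 12 = 0.90d
- fitted week-12 difference = mean + 6 x slope = 0.75d + 0.45d = 1.20d

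| True effect at weeks 0, 4, 8, 12 | Slope x 12 | Fitted week-12 difference |
|---|---|---|
| 0, d/3, 2d/3, d | 1.00d | 1.00d |
| 0, d, d, d | 0.90d | 1.20d |
| 0, d/2, d, d | 1.05d | 1.15d |
| 0, 0, 0, d | 0.90d | 0.70d |

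If D0 is left out of the response, the profile (d, d, d) over weeks 4, 8 and 12 has slope 0, so a sustained benefit gives an interaction of zero.

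**The case against.** A reader might infer that the plan understates the week-12 effect. The documents do not support that. Under randomisation, omitting baseline costs precision but leaves the week-12 mean difference unbiased. For linear time, the sign of the error depends on the effect's course and on the contrast reported: the week-4 plateau gives 0.90d on one contrast and 1.20d on the other.

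A reader might also infer that baseline is excluded. That goes too far as well. The planned adjusted regression has unlisted covariates, so own baseline is unnamed rather than ruled out, and the list without it belongs to the primary outcome. If D0 is a response in the longitudinal model, baseline information is used there. Under compound symmetry and a linear effect, slope x 12 is then less precise than the unadjusted test at rho = 0.3, but more precise at 0.5 and 0.7. Compound symmetry itself leaves out the random-slope variance that the plan specifies.

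Further limits stand. Linear time is inferred from the random slope; with categorical visits, the week-12 interaction would not have this bias. An early plateau has no time-course data behind it, and the protocol describes treatment periods 2 and 3 as following period 1. The correlation is assumed, and the variance ratios apply only if the test uses week-12 values. The pre-test governs only the unadjusted comparison. The outcomes are exploratory.

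None of this supplies what is missing: a designated analysis, a named baseline covariate, a time coding and a week-12 contrast.

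**Conclusion.** The point holds as one of specification and efficiency. Three analyses are planned for the same outcomes and none is designated as the result.

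- **Precision:** if it uses week-12 values, the unadjusted test has 10% to 96% more variance than ANCOVA for rho between 0.3 and 0.7, and 33% more at 0.5. It remains unbiased.
- **Week-12 effect:** if time is linear, the profiles shown give 0.90d to 1.05d as slope x 12 and 0.70d to 1.20d as the fitted difference. The interaction is zero for a week-4 plateau if D0 is left out. The error has no fixed direction.
- **Pre-test:** the unadjusted p-value may belong to a rank comparison while the reported effect is a difference in means.

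The primary conclusion does not depend on this. The change should be made because it improves the secondary results at almost no cost.

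**What to change.** For each of IBS-SSS, GIQLI and EQ-5D, prespecify one repeated-measures model on weeks 4, 8 and 12 with group, categorical visit, group-by-visit, the outcome's own D0 value, baseline-by-visit and centre. An equivalent constrained-baseline model, with D0 as a response and a common baseline mean across groups, would serve as well. Name the adjusted week-12 difference in scale units, with its 95% CI, as the result. Delete the test selection by Shapiro-Wilk and Fisher-Snedecor, and align the protocol's Statistical methods with SAP 2.4 on the model and the effect scale.

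The cost is SAP and protocol wording and analysis code. The visit schedule already provides the data, and no extra patients or assessments are needed.
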